### Study design

A combination of observational quantitative and qualitative study designs will be used to measure the health and healthcare utilization outcomes of a primary care IM clinical model. Where possible, the clinical and economic impacts seen in this IM model will be compared to data available from one or more comparison groups (see discussion of comparison groups below). When comparison group data are not available for outcomes —e.g., for most of the self-report data and for the medical records data—baseline values for clinic participants will be compared to those measured during and after treatment. Table 1 shows the types of comparisons planned for each outcome data category for the observational study.

**Table 1 T1:** Outcomes measured for the UAIHC

	**Frequency of measurement**	**Pre/post comparisons**	**Comparisons against control group(s)**
Healthcare utilization and costs	One year prior and one year post-study enrollment	X	X^*^
Diet quality	BL, 3, 6, and 12 months	X	X^**^
Exercise	BL, 3, 6, and 12 months	X	X^**^
Patient satisfaction	3, 6, and 12 months	X	X^***^
Self-report health outcomes	BL, 3, 6, and 12 months	X	
• Self-efficacy			
• Stress			
• Sleep quality			
• Pain			
• Fatigue			
• Depression			
• Anxiety			
• Health-related quality of life			
• Well being			
• Work productivity			
• Condition-specific			
• outcomes			
Medical records data	3, 6, and 12 months	X	

BL = baseline (clinic enrollment).

^*^Primary outcome; comparison is to two matched control groups.

^**^Comparison here is to national (and where available statewide) averages from the Center for Disease Control and Prevention’s Behavioral Risk Factor Surveillance System (BRFSS) survey [51].

^***^Comparison here is to national and regional norms using the Consumer Assessment of Healthcare Providers and Systems (CAHPS) Adult Visit Survey 2.0 data [50].

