### Comparison group(s)

Data from UAIHC patients will be compared, where possible, to those of patients seen in other clinics. The primary outcome, total healthcare utilization, will be obtained from healthcare claims data for patients whose employers have given access to those data. For these patients, matched comparison groups will be developed using two different matching algorithms applied to de-identified claims data for non-UAIHC patients. One will use a straight matching algorithm based on age and gender, and the other will use propensity scores to match [49]. At least one of the participating employers also has employee lab values available. Where these data are available, the same matched comparison groups will be used to compare changes in key lab values seen across groups. Finally, several of the self-report measures have national and regional comparisons available. The measures of patient experiences and patient satisfaction are drawn from the Consumer Assessment of Healthcare Providers and Systems (CAHPS) Adult Visit Survey 2.0 [50]. The CAHPS website contains data on the results of these questions nationally, by region, and by physician specialty. The results seen for UAIHC participants will be compared to those seen by all providers nationally, by all providers in the West region, and by family practice doctors nationally. The measures of diet and exercise quality come from the Center for Disease Control and Prevention’s Behavioral Risk Factor Surveillance System survey [51]. National and statewide averages are available for these items. Unfortunately, no other secondary data sources are available for comparisons. For all other outcomes, UAIHC participants will act as their own controls by comparing their outcome measures over time to baseline.

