### Data collected from medical records

These data will be collected at 3, 6, and 12 months. A medical records abstraction form will be used to collect the following from the patient chart for the period since the last outcomes data collection point. The results of any of the following lab tests will be captured: fasting glucose, lipid panel, thyroid stimulating hormone (TSH), glycosylated hemoglobin (HbA1c), inflammatory markers (erythrocyte sedimentation rate and high-sensitivity C-reactive protein), vitamin D status, and measures of anemia (hemoglobin, hematocrit, and mean corpuscular volume). Also captured will be each patient’s diagnosis(es), systolic and diastolic blood pressure, heart and respiratory rates, weight, waist circumference, body fat composition, smoking status, and whether the patient is on hypoglycemic, dyslipidemia, or hypertension medication. Composite scores (10-year cardiovascular disease (CVD) event risk [70], 10-year CVD mortality risk [71], and metabolic syndrome diagnosis [72]) will be captured from the chart when recorded, or will be calculated. Forced vital capacity and forced expiratory volume will be captured for participants with pulmonary disease.

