The fourth and fifth analyses will be the main outcome studies. The fourth study will be a prospective cohort study of the changes in outcomes from baseline to one year for all patients in the outcomes sample. The primary outcome for this analysis will be health-related quality of life measured in three ways (SF-6D [78], and the physical and mental component summary scores, all derived from the SF-12), with the other outcomes as secondary measures. The main comparison will be baseline to 12-month outcomes and the univariate analyses will use paired *t* tests for continuous data, and use the McNemar test for frequencies [79]. The data will also be examined for patterns of change over time in key outcomes, and the determinants of those patterns, using hierarchical linear modeling (HLM) techniques [80-82]. Fidelity measures with significant changes over time will be used as covariates [24] in these models, as well as other explanatory variables such as demographics, participants’ membership level and baseline diagnoses. If participant numbers for each of the five targeted condition allow, condition-specific outcomes will be examined for each. These same analyses will be applied to other secondary outcomes such as CVD event [70] and mortality [71] risk.

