The fifth analysis will focus on the subset of patients for which health insurance claims data are available and will utilize a matched comparison design. Prior to analysis all claims data for each individual (treatment and comparison groups) will be aggregated (by summation) into per health plan member per month (PMPM) totals of paid amounts (the amount paid by the health plan to the practitioner) for each of the following cost categories: total, inpatient, outpatient, emergency room, physician, and pharmaceutical claims. Similarly, the numbers of outpatient visits, hospital stays and emergency department visits will also be aggregated for each individual. The primary outcome will be total cost. Two comparison groups from de-identified claims data will be created—one using simple matching (e.g., by age and gender) and one using propensity scores [49]. After the comparison groups have been selected, simple descriptive analyses will show average PMPM costs and healthcare utilization (including standard deviations and other measures of dispersion) pre- and post- enrollment (or an equivalent date for the comparison groups) by gender, age, baseline diagnosis and by treatment and comparison group. Because cost data tends to be highly skewed, average PMPM costs and healthcare utilization pre/post enrollment, and the change in costs and utilization pre/post between the treatment and each of the comparison groups will be reported as mean differences with confidence intervals calculated using bootstrap methods [83,84]. Because of the number of data points for each patient (e.g., up to 12 PMPM values pre-enrollment and 12 post-enrollment), HLM [80-82] will be used to estimate the pattern of change in healthcare utilization and costs over time, and to explore the determinants of those patterns. Fidelity measures with significant changes over time [24], demographics, participants’ membership level and baseline diagnoses will be included as covariates in these models. Finally, changes in costs between groups will be compared to changes in patients’ CVD risk.

Results for the last two analyses will be reported following the Strengthening the Reporting of Observational Studies in Epidemiology (STROBE) guidelines [85]. For all outcomes, the estimated treatment effects will be reported using their original outcome scale and including confidence intervals.

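### The uncontrolled 12-month change in 10-year CVD risk scores includes one year of ageing if age is a score input, which shrinks any benefit and can mask or reverse a modest one

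*Protocol article*

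**What the plan says.** In the Protocol article, the fourth analysis (section Analysis) is a within-patient cohort comparison: "The main comparison will be baseline to 12-month outcomes and the univariate analyses will use paired *t* tests for continuous data". Patterns over time are examined by HLM with demographics, membership level, diagnoses and fidelity measures as explanatory variables. The paragraph ends by extending the plan to the risk scores: "These same analyses will be applied to other secondary outcomes such as CVD event [70] and mortality [71] risk".

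The section Data collected from medical records defines both as 10-year composite scores that "will be captured from the chart when recorded, or will be calculated". It identifies them by literature reference and does not list their inputs. It does not say which age is entered at follow-up.

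No comparison group is planned for these scores. Study design names the outcomes without comparison data as those "for most of the self-report data and for the medical records data", and Table 1 has no control-group entry for medical records data. Comparison group(s) reserves the matched groups for claims and, where available, key lab values, and adds: "For all other outcomes, UAIHC participants will act as their own controls by comparing their outcome measures over time to baseline".

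The change in CVD risk is used again in the fifth analysis, which closes with "Finally, changes in costs between groups will be compared to changes in" the CVD risk of patients.

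**The concern.** A paired test asks whether the mean change is zero. For a 10-year absolute risk that depends on age, zero is not what an inert clinic would produce. Patients are a year older at month 12, so the expected change with every modifiable factor constant is above zero. With no comparison group, nothing in the contrast cancels that term.

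Demographic covariates in the HLM do not remove it either. Baseline age explains differences between patients, whereas the ageing term lies within each patient and coincides with follow-up time, so it is absorbed into the time effect being estimated.

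The article says that estimated treatment effects will be reported for all outcomes. For these two, the reported effect would be the sum of the clinic's effect and a year of ageing, with ageing acting against the clinic.

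**Working it through.** **The plan's own figure.** The documents give no power figure for CVD risk. The only sample-size statement (Outcomes sample) is 200 patients for d = 0.20, power 0.80 and alpha 0.05 on total costs. As a one-sample or paired calculation with two-sided alpha, n = ((1.960 + 0.842)/0.20)² ≈ 197 (199 by noncentral t), and power at 200 is 0.80, so it reproduces. I use 200, and the expected enrolment of 500, only as reference sizes. The number of patients with paired CVD scores is not given.

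**Assumptions, none from the documents.** Age is an input to both scores. With risk factors unchanged, the score rises by a relative g = 3% to 10% per year of age. (A risk that doubles every 8 to 15 years of age gives 2^(1/8) − 1 = 9.1% to 2^(1/15) − 1 = 4.7%, inside that range.) Mean baseline risk is m = 10%, and the SD of the 12-month change is 4 points.

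**Formulas.**
- Drift from ageing alone = m × g.
- Relative reduction needed to cancel it = 1 − 1/(1 + g).
- Observed change with a true relative benefit b = m × [(1 + g)(1 − b) − 1].
- Chance of significance: two-sided paired t test at 0.05, noncentrality √N × |mean change|/SD.

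**Ageing alone, no true change.**

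| g | Drift (points) | Reduction to break even | Significant worsening, N=200 | N=500 |
|---|---|---|---|---|
| 3% | +0.30 | 2.9% | 0.18 | 0.39 |
| 5% | +0.50 | 4.8% | 0.42 | 0.80 |
| 7% | +0.70 | 6.5% | 0.69 | 0.97 |
| 10% | +1.00 | 9.1% | 0.94 | 1.00 |

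Check of the first row: √200 × 0.30/4 = 1.06, and P(Z > 1.96 − 1.06) = 0.18.

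**With a true benefit (observed change in points).**

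| g | b = 5% (age-fixed −0.50) | b = 10% (age-fixed −1.00) | b = 20% (age-fixed −2.00) |
|---|---|---|---|
| 3% | −0.215 | −0.73 | −1.76 |
| 5% | −0.025 | −0.55 | −1.60 |
| 7% | +0.165 | −0.37 | −1.44 |
| 10% | +0.45 | −0.10 | −1.20 |

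For b = 10% at N=200, power is 0.94 with age fixed, and 0.73, 0.49, 0.26 and 0.06 down the rows with age advancing. For b = 20% it is at least 0.99 throughout.

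**Sensitivity of the false-worsening figure (N=200, g from 3% to 10%).** At mean risk 10%: 0.56–1.00 with SD 2, and 0.11–0.65 with SD 6. With SD 4: 0.08–0.42 at mean risk 5%, and 0.35–1.00 at mean risk 15%. The size depends heavily on the assumptions; the direction does not.

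**The case against.** A reader might infer that ageing hides or reverses any benefit of the clinic. The documents and the arithmetic do not support that. Only a benefit near or below the one-year drift is masked or reversed. In the table a 10% reduction keeps its direction throughout, though at g = 10% it is almost invisible, and a 20% reduction is still detected. Nor do the documents show that age is in either score. That is an assumption, and it limits confidence.

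Other points have weight:

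- **Modifiable factors are measured directly.** Blood pressure, lipids, glucose, HbA1c, weight, waist and smoking are abstracted, so improvement can be seen without the composite. This stands and lowers the practical harm.
- **Other forces act on an uncontrolled change.** Regression to the mean could push the scores the other way, so the net bias is unknown. This stands. Ageing is nevertheless one component of known direction that can be removed. By itself it cannot create a false claim of benefit.
- **The cost comparison has no stated method.** If it is an association across patients, a near-uniform shift largely drops out. The concern applies there only if mean changes are set side by side.
- **Change in actual absolute risk is a legitimate quantity, and the scoring convention could sit in a fuller plan.** The first part is true, but that quantity is not the clinic's effect. As for the second, the article does not leave the analysis open: it fixes the outcome, the contrast and the test, and followed as written these include the ageing term.

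**Conclusion.** The point holds, conditional on age entering the scores. Under the stated analysis the estimated 12-month change in 10-year CVD event and mortality risk is biased upward by one year of ageing. Any benefit is attenuated. One below about 3–9% relative (for risk growth of 3–10% per year of age) is reversed, one close to that size is masked, and clearly larger ones are reduced but remain visible. At mean risk 10% and SD of change 4 points, ageing alone gives a significant worsening in about 18–94% of studies at N=200, against a nominal 5%. The mean risk, SD and growth rate are all assumed.

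Severity is low to moderate. These are secondary outcomes. Quality of life, total cost and the sample size of 200 are not touched.

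**What to change.** Add one sentence to the fourth analysis: for the paired and HLM analyses of change, follow-up CVD event and mortality scores are computed with age held at its baseline value and only the modifiable inputs updated, wherever the abstracted inputs are available at both times; the score at actual age is reported descriptively. Apply the same score in the fifth analysis if mean changes in cost and CVD risk are set side by side.

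The drift is then zero by construction, and the result stays in percentage points of 10-year risk. The article already provides for calculating scores that are not recorded, so the work is mainly recalculation. There are two costs. The fixed-age score will differ from the value in the chart. Patients with only a chart-recorded score and incomplete inputs cannot be recalculated, so the number excluded for that reason should be reported. The change does not address regression to the mean or other influences on an uncontrolled comparison.

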### Setting and Participants

Data used in the evaluation will be gathered from eligible and consenting participants who are also patients enrolled at the University of Arizona Integrative Health Center (UAIHC), an integrative medicine adult primary care clinic in Phoenix, Arizona. Operated in conjunction with District Medical Group, Inc., UAIHC is financed through insurance reimbursements and a patient membership fee structure. At present, two major employers in the Phoenix area pay a portion of the membership fee for their employees who elect UAIHC as their primary care provider. There are four groups of study participants. The first (and main) group consists of eligible participants from the clinic patient population for whom clinical and cost outcomes will be tracked indicating the impact of the UAIHC clinic (n = 500). The second and third groups consist of clinic patients (n = 180) and clinic personnel (n = 15-20) from whom fidelity data will be collected. The fourth group is made up of the patients (n = 8) whose path through the clinic will be studied in detail using qualitative methods. The clinic patients involved in the outcomes study sample may or may not be included in the fidelity patient sample, and vice versa. However, the qualitative data sample is expected to be a subset of the outcomes sample.

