### Intervention

The IM professional practice model for primary care utilizes an inter-professional, physician-led, integrative clinical team to provide patient-centered care. UAIHC services include conventional medical care, lifestyle interventions, and evidence-based CM interventions. In particular, services include longer visits with providers, a commitment to health, a partnership agreement with the health care team, increased access via telephone and email in addition to in-person visits and classes, and a wider range of services including nutritional counseling, acupuncture, chiropractic care, stress-reducing mind-body approaches, and health coaching. In addition to individual appointments, group visits and health promotion classes are offered (e.g., nutrition, yoga, meditation). Emphasis is placed on motivating and supporting lifestyle behavior change. Although patients with a wide variety of diagnoses will be eligible and included in the study, outcomes for patients with the following five conditions (low back pain, fibromyalgia, other musculoskeletal conditions, metabolic syndrome and diabetes, and cardiovascular disease) will be analyzed separately where possible.

The UAIHC business model uses a hybrid financing approach that utilizes usual insurance reimbursements supplemented by a patient membership fee. The membership fee covers a certain number of CM practitioner visits, health coaching visits, and classes (a “class” may comprise a series of individual sessions). Three fee tiers have been established: 1) basic bundle (5 visits with the patient’s choice of CM practitioners, 2 visits with a health coach, and 2 groups or classes); 2) core (10 visits with the CM practitioners of choice, 4 health coach visits, and 4 groups or classes); and, 3) expanded (20 visits with CM practitioners, 8 visits with a health coach, and 8 groups or classes). For some members, this fee is partially offset by collaborating employers who offer UAIHC as an employee health benefit option. (Grant funding supports the costs of this study for those participants employed with these collaborators).

According to its business plan, the IM primary care practice model will follow IM principles [44] as well as the principles of primary care [45,46] and the patient-centered medical home [47]. More detail on the IM primary care practice model is presented in Dodds et al [48].

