### Data Collection

For the outcomes evaluation, data will be collected from patient charts and self-reports at four intervals—baseline (initial clinic visit), and at 3-, 6-, and 12-month follow up periods. Participants will receive a reminder email one week before each data collection due date. Baseline data will be due within one week of enrollment. In the email they will be directed to a secure website where they can access and complete the outcomes data collection instrument. If participants have not entered their data within 3 days of their due date, they will receive another reminder email, and those who have not entered their data within another 3 days of their due date will receive a call from the UA Study Coordinator. Healthcare utilization and cost data from healthcare claims will be obtained from their employer with study participant consent. These data will be collected for one year before and one year after clinic enrollment approximately 3 months after the 12-month follow up period to allow time for all incurred claims to be recorded. De-identified claims data for the comparison groups will be collected for the same period of time with “baseline” being defined by the average start date of study participants.

Because the intervention may change over time as clinic operations start up and mature [21], fidelity monitoring data will be collected monthly from study start for 6 months, then quarterly for 6 months, and then semi-annually. Patient-reported fidelity data will be gathered on a single randomly chosen day of the last week of the data collection month from all patients seen at the UAIHC clinic that day. This day will be selected by the UA research team using a simple computer generated randomization scheme and delivered to the UA Study Coordinator the week before the data collection week. A self-administered patient version of the “How is UAIHC doing?” questionnaire will be used for patients. For clinic personnel, fidelity data will be collected during the last week of each fidelity data collection month using an online self-administered practitioner and staff version of the “How is UAIHC doing?” questionnaire. Data from audits of randomly selected, de-identified patient charts and of administrative records will also be used to assess indicators of model implementation.

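### The primary total cost counts only what the health plan pays on claims, so it omits the UAIHC membership fee and can overstate savings

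*Protocol article*

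**What the plan says.** All places are in the protocol article.

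- **Analysis (fifth analysis).** Claims are summed per member per month (PMPM) into "totals of paid amounts (the amount paid by the health plan to the practitioner) for each of the following cost categories". The categories that follow include a total. The section then states: "The primary outcome will be total cost". Membership level appears only as a covariate in the hierarchical models.
- **Data Collection.** The cost source is claims: "Healthcare utilization and cost data from healthcare claims will be obtained from their employer with study participant consent". Comparison group(s) and Health Insurance Claims Data also draw this outcome from claims, with controls taken from de-identified records of non-UAIHC patients.
- **Intervention.** "The UAIHC business model uses a hybrid financing approach that utilizes usual insurance reimbursements supplemented by a patient membership fee". On what the fee buys: "The membership fee covers a certain number of CM practitioner visits, health coaching visits, and classes". There are three tiers. On who pays: "For some members, this fee is partially offset by collaborating employers who offer UAIHC as an employee health benefit option".
- **Setting and Participants.** "UAIHC is financed through insurance reimbursements and a patient membership fee structure", and "two major employers in the Phoenix area pay a portion of the membership fee for their employees".
- **Aims.** The opening of Methods/Design gives the purpose as evaluating clinical and cost effectiveness. The Abstract and the Discussion present the study as a test of whether such a model can reduce healthcare cost and be financially sustainable.

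**The concern.** The outcome called total cost leaves out one of the two revenue streams that finance the clinic. That stream pays for services which help to distinguish the model from conventional primary care. Members begin to bear the fee when they join, and matched controls never do. It is therefore a post-enrolment cost in one group only, and it does not cancel in a pre/post comparison between groups.

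At stake is the main economic conclusion. A lower plan-paid figure for UAIHC members could mean that care became cheaper. It could also mean that some care is now paid for through the fee. The outcome as defined cannot separate the two, while the aims invite the first reading.

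**Working it through.** **1. The plan's own figure.** Outcomes sample says 200 patients suffice to detect d = 0.20 in total costs with power 0.80 at alpha 0.05. For a two-sided test of a mean paired change:

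n = ((1.960 + 0.842) / 0.20)² ≈ 196.2, so 197. The t-based version gives 199, and power at 200 is 0.804.

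The figure reproduces on that basis. The present point does not depend on it. It is used below only to set a scale of 0.20 SD.

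**2. Where each payment is counted.**

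| Payment | In the primary total cost? | Basis |
|---|---|---|
| UAIHC care reimbursed by insurance | Yes | Analysis |
| Membership fee, patient share | No | Intervention; Analysis |
| Membership fee, employer share | Not stated to be; taken as no | Setting and Participants; Analysis |
| Other out-of-pocket spending, either group | No | Analysis |

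The self-report items do not fill the gap. The four utilization items count services (primary care only if outside UAIHC) and ask nothing about spending. Membership level as a covariate adds no dollars to the outcome, and controls have no membership level.

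**3. Direction.** Let D be the UAIHC-minus-control difference in pre/post change, in dollars PMPM, and F the mean fee PMPM. Then

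D(overall) = D(plan-paid) + F + D(other out-of-pocket).

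F is positive for members after enrolment and zero for controls. Leaving it out moves the result toward savings by exactly F. The last term is unobserved and its sign is unknown. If it is set aside, a plan-paid saving of S is an overall saving only when S exceeds F.

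**4. Size: illustration only.** The article gives no fee, bundle period or cost SD. From the tiers, the bundled services number 5 + 2 + 2 = 9 (basic), 10 + 4 + 4 = 18 (core) and 20 + 8 + 8 = 36 (expanded). Suppose the bundles are annual and each service is worth $30 to $100. Services × value / 12 then gives:

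- basic: $22.50 to $75 PMPM
- core: $45 to $150 PMPM
- expanded: $90 to $300 PMPM

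This values the services, not the fee, so it gives only an order of magnitude. Against the design effect, with an assumed fee of $25 to $150 PMPM:

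| Assumed SD of PMPM cost | 0.20 SD | Fee in SD units |
|---|---|---|
| $250 | $50 | 0.10 to 0.60 |
| $500 | $100 | 0.05 to 0.30 |
| $1,000 | $200 | 0.025 to 0.15 |
| $1,500 | $300 | 0.017 to 0.10 |

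The omitted fee could exceed the effect the study is sized to detect, or be a small part of it.

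**The case against.** The strongest reply is that plan-paid PMPM is a legitimate outcome and is openly defined. The article says in parentheses whose payment is meant, lists the total among claims categories, and measures it identically in both groups. For the health-plan perspective the contrast is correct as it stands. This is right, and it is why the measure need not be abandoned. But the article names no perspective, labels the figure total cost, ties it to cost effectiveness, and does not list the omission among its limitations.

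A reader might infer more than the documents support, in four ways.

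- *That the study will report cost shifting as savings.* Shifting requires fee-funded services to replace services the plan would have paid for. No section says these employers' plans cover acupuncture, chiropractic care, coaching or classes, and a supplement to reimbursement fits added services equally well. If they are additions, plan-paid cost does not fall through shifting, though the fee is still uncounted.
- *That the fee funds the whole intervention.* Financing is hybrid, and UAIHC care billed to insurance is counted.
- *That the omitted amount is known to be large and everything uncounted favours UAIHC.* Every dollar value above is assumed. Cost sharing and self-paid complementary care are uncounted in both groups and in both periods, so one-sidedness holds for the fee alone.
- *That a fee-inclusive cost should replace the primary outcome.* This would add a non-claim item for members after enrolment only. Comparable spending cannot be seen for de-identified controls or in the pre-enrolment year. The result would be neither a payer nor a societal cost, and could lean against UAIHC by an unknown amount.

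These limits stand. They restrict the size, the wording and the remedy. They do not remove the omission or its direction.

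**Conclusion.** The concern holds in this form: the primary total cost is a plan-paid cost, and it leaves out a fee that only UAIHC members bear, and only after enrolment. The between-group contrast therefore understates the model's cost by the mean fee PMPM, and can present services moved from claims to the fee as savings. The omission follows from the stated definition of the primary outcome and is not a detail that a fuller plan would ordinarily settle.

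The amount cannot be calculated from the documents. The conclusion rests on one inference: that the fee, including the employer share, does not appear among the claims. The article separates reimbursement from the fee but does not say how the employer share is recorded. Whether shifting occurs, and how far, depends on substitution that the documents do not describe.

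**What to change.** 1. Name the primary outcome of the fifth analysis plan-paid PMPM cost, and limit its conclusion to the health-plan perspective.
2. Prespecify a co-reported fee-inclusive total: plan-paid amount plus the patient and employer fee for the member's tier, spread over the post-enrolment months. State the fee schedule and bundle period, and confirm that no employer share is already in the claims.
3. Base any statement on cost effectiveness or lower cost of healthcare on both results.
4. State as a limitation that other out-of-pocket spending is unobserved in both groups and in the pre-enrolment year.

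The cost is small: changed wording, a fee lookup by tier (membership level is already planned as a covariate) and one more run of the planned bootstrap comparison. The primary measure stays identical in both groups. The downside for the sponsor is a less favourable second cost figure.
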